## Abstract

**Background:**

Following discharge home from the ICU, patients often suffer from reduced physical function, exercise capacity, health-related quality of life and social functioning. There is usually no support to address these longer term problems, and there has been limited research carried out into interventions which could improve patient outcomes. The aim of this study is to investigate the effectiveness and cost-effectiveness of a 6-week programme of exercise on physical function in patients discharged from hospital following critical illness compared to standard care.

**Methods/Design:**

The study design is a multicentre prospective phase II, allocation-concealed, assessor-blinded, randomised controlled clinical trial. Participants randomised to the intervention group will complete three exercise sessions per week (two sessions of supervised exercise and one unsupervised session) for 6 weeks. Supervised sessions will take place in a hospital gymnasium or, if this is not possible, in the participants home and the unsupervised session will take place at home. Blinded outcome assessment will be conducted at baseline after hospital discharge, following the exercise intervention, and at 6 months following baseline assessment (or equivalent time points for the standard care group). The primary outcome measure is physical function as measured by the physical functioning subscale of the Short-Form-36 health survey following the exercise programme. Secondary outcomes are health-related quality of life, exercise capacity, anxiety and depression, self efficacy to exercise and healthcare resource use. In addition, semi-structured interviews will be conducted to explore participants’ perceptions of the exercise programme, and the feasibility (safety, practicality and acceptability) of providing the exercise programme will be assessed. A within-trial cost-utility analysis to assess the cost-effectiveness of the intervention compared to standard care will also be conducted.

**Discussion:**

If the exercise programme is found to be effective, this study will improve outcomes that are meaningful to patients and their families. It will inform the design of a future multicentre phase III clinical trial of exercise following recovery from critical illness. It will provide useful information which will help the development of services for patients after critical illness.

**Trial registration:**

ClinicalTrials.gov NCT01463579

## Background

Following discharge from the ICU, patients often suffer from reduced physical function, exercise capacity, health-related quality of life and social functioning which may continue for up to 5 years following discharge home from hospital [1-5]. In a systematic review of 53 studies (10 multicentre) reporting health-related quality of life outcomes at least 12 months after discharge from the ICU, critically ill patients had a lower health-related quality of life than an age- and gender-matched population [6]. The worst reductions in quality of life were seen in cases of severe acute respiratory distress syndrome, prolonged mechanical ventilation, severe trauma, and severe sepsis. There is usually no support to address these longer term problems specific to critical illness. Rehabilitation after critical illness is recognised as a prominent therapeutic objective for the future for this population in the recent National Institute for Health and Care Excellence Guidelines [7].

There is evidence to support the rehabilitation of critically ill patients within the ICU [8-10], but there is a paucity of literature to support rehabilitation following discharge from intensive care and particularly following discharge from hospital. It is also unclear what components should be included in post-hospital discharge rehabilitation. At the time of concept of this trial, studies evaluating post-hospital discharge rehabilitation following critical illness showed discordant results [11-14]. Jones and colleagues [11] conducted a randomised controlled trial comparing a rehabilitation manual, which included advice on psychological, psychosocial and physical problems and a self-directed exercise programme, to standard care. While there was significant improvement in the Short-Form-36 Health Survey (SF-36) physical function scores and reduced depression, the effects on outcomes such as functional ability or exercise capacity were not measured. McWilliams and colleagues [12] assessed the effect of a 6-week rehabilitation programme, which included education and supervised exercise classes as well as unsupervised home exercise sessions in a cohort group. It did not include blinded outcome assessment. Significant improvement in physical function using the six-minute walk test (6MWT) and the incremental shuttle walk test and the hospital anxiety and depression scores were found.

Two trials failed to demonstrate improved outcomes in the intervention group compared to standard care [13,14]. An 8-week home-based physical rehabilitation programme failed to show improvements in physical function (6MWT) and health-related quality of life (SF-36) compared to standard care [13]. Potential reasons reported for this lack of difference include a lack of compliance in the intervention group due to minimal supervision and inadequate training intensity. A nurse-led follow-up programme reported no difference in outcomes compared to standard care [14]. It is difficult to determine whether the results of this study were affected by the limited nature of the intervention which did not appear to include elements of rehabilitation that would target important physical and non-physical problems in this population.

In these studies [11-14], patients’ length of time in ICU and/or duration of mechanical ventilation were relatively short. It is debatable whether this patient cohort would have significant disability or reasonably represent the population that would benefit most from rehabilitation interventions. The present study, therefore, plans to address the gap in current knowledge by investigating the effectiveness of an exercise programme on physical function in patients discharged from hospital following critical illness compared to standard care. To overcome the limitations of previous studies, two out of three exercise sessions per week, for a 6-week period, will be supervised and we aim to recruit patients who have had a longer time on mechanical ventilation than in previous studies (greater than 96 hours) as they may be at higher risk of longer term sequelae after critical illness. In addition, we will assess the suitability of the programme, both from the patient’s perspective and a healthcare cost perspective.

### Aim

The aim of this study is to investigate the effectiveness and cost-effectiveness of a 6-week programme of exercise on physical function in patients discharged from hospital following critical illness compared to standard care.

### Objectives

The objectives are: (i) to investigate the effectiveness of a 6-week programme of exercise on physical function, health-related quality of life, exercise capacity, anxiety and depression and self efficacy to exercise in patients discharged home from hospital following critical illness compared to standard care; (ii) to determine the feasibility (safety, practicality and acceptability) of providing a 6-week programme of exercise for patients discharged from hospital following critical illness; (iii) to explore participants’ perceptions of the 6-week exercise programme; (iv) to examine medium-term (6-months) effects of the exercise programme; and (v) to evaluate the cost-effectiveness of the exercise programme.

## Methods/Design

The planned design of this multicentre prospective phase II, allocation-concealed, assessor-blinded, randomised controlled clinical trial adheres to the Standard Protocol Items Recommendations for Interventional Trials guidelines for clinical trial protocols [15] and the Consolidated Standards of Reporting Trials statement for reporting randomised controlled trials [16] (Figure 1).

**Figure 1 F1:**
[figure not shown]
**Consolidated Standards of Reporting Trials (CONSORT) 2010 study flow diagram.** CONSORT flow diagram for effectiveness of a programme of exercise on physical function in survivors of critical illness following discharge from the ICU: study protocol for a randomised controlled trial.

### Study approvals

The study protocol has been approved by the Northern Ireland Research Ethics Committee (REC reference 11/NI/0115) and research governance approval has been granted by the five Health and Social Care Trusts in Northern Ireland. The study is registered with ClinicalTrials.gov registry (NCT01463579) [17]. It is sponsored by the University of Ulster and the Belfast Health and Social Care Trust, and has been adopted by the Northern Ireland Clinical Research Network (Critical Care and Respiratory Health). It is supported by the Northern Ireland Clinical Trials Unit (NICTU), a UK Clinical Research Collaboration registered clinical trials unit.

### Study population

To be eligible for recruitment into the study patients must be aged 18 years or older, have had an ICU admission requiring mechanical ventilation greater than 96 hours, planned discharge to home (self-care/carer), be willing and able to participate in exercise and deemed medically fit to take part in the intervention. Patients will be excluded if they meet any of the following criteria: declined consent or unable to give consent; inability to participate due to, for example, any neurological, spinal or skeletal dysfunction affecting ability to exercise; cognitive impairment affecting ability to consent, participate in the intervention or complete questionnaires; participation in another structured rehabilitation programme due to ongoing chronic disease; any medical contraindication to participation in an exercise programme.

### Recruitment

Patients in the ICUs will be prospectively screened. All eligible consecutive patients will be given written information about the study following discharge from critical care. They will be approached to enquire if they are interested and willing to take part in the study. A screening log of all non-recruited patients and the reason for exclusion will be maintained. If willing to participate, patients will be asked to provide written informed consent by a trained member of the research team prior to commencing the study. Participants will be randomised to the exercise programme or standard care. A randomisation schedule will be produced using permuted block randomisation technique, at a 1:1 ratio. Variable block sizes are used to ensure blinding. The randomisation schedule will be generated using nQuery Advisor by the clinical trials unit (NICTU). Allocations are done centrally by the NICTU (allocation concealment). The randomisation service will allocate a unique trial identification number to each participant in accordance with the computer-generated study randomisation schedule. In order to maintain confidentiality, all case report forms, study reports and all communication regarding the study will identify participants using the unique identification numbers. Participants allocated to the programme of exercise will commence as soon as possible.

### Sample size

There is limited data available in this specific research area in order to conduct a formal sample size calculation. Jones and colleagues [11] demonstrated an approximate 24% improvement in the physical function score of the SF-36 with a rehabilitation manual which included a self-directed exercise programme. With the limited data available we have used a more general method to calculate the sample size [18], which would result in 52 patients (26 per group) for a large effect size. On the basis of our previous experience and published data we have estimated a loss of 25% after randomisation [19]. Thus, this study will aim to recruit up to 68 patients (34 in each group), or until we achieve 52 (26 per group) completed datasets at 6 weeks over the proposed 36-month recruitment period. Participants will be withdrawn on request, if there are adverse effects arising from the exercise programme, or due to inability to perform baseline assessment.

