### Statistical methods/analyses

For continuously distributed outcomes, differences between groups will be tested using independent samples *t*-tests, analysis of variance and analysis of covariance with transformations of variables to normality if appropriate, or non-parametric equivalents. Chi-square tests (or Fisher’s Exact tests) will be used for categorical variables. Efficacy of intervention will be analysed on an intention-to-treat basis. A *P* value ≤0.05 will be considered significant. A single final analysis is planned at the end of the trial. Baseline variables will be recorded to demonstrate that the groups are comparable; if this is not demonstrated, *post-hoc* adjustments to correct for differences will be applied. Every effort will be made to collect outcomes from patients, even those who drop out of the exercise programme. Every effort will be made to minimise missing baseline and outcome data in this trial. The level and pattern of the missing data in the baseline variables and outcomes will be established by forming appropriate tables and the likely causes of any missingness will be investigated. This information will be used to determine whether the level and type of missing data has the potential to introduce bias into the analysis results for the proposed statistical methods, or substantially reduce the precision of estimates related to treatment effects. If necessary, these issues will be dealt with using multiple imputation or Bayesian methods for missing data as appropriate. The power calculations and methodology for data analysis have been reviewed and confirmed by the study statistician. Until data analysis is completed the study statistician will be unaware of whether the participant received the intervention or standard care.

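### Inflating 52 completers for a 25% loss gives 70, not the stated 68, and the recruitment sentence does not say which limit governs

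*Protocol article*

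**What the plan says.** All the figures stand in the Sample size section of the protocol article. Citing limited data, the authors write that "we have used a more general method to calculate the sample size", "which would result in 52 patients (26 per group) for a large effect size". They then state that "we have estimated a loss of 25% after randomisation", on the basis of earlier experience and published data. The recruitment figure is presented as the consequence of these two inputs: "Thus, this study will aim to recruit up to 68 patients (34 in each group), or until we achieve 52 (26 per group) completed datasets". The completed datasets are those at 6 weeks, within a proposed 36-month recruitment period.

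The section gives no numerical effect size, power or sidedness. The section on statistical methods adds only that a P "value ≤0.05 will be considered significant". The article does not say whether 68 is a hard limit, or what happens if 68 have been randomised and fewer than 52 datasets are complete.

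**The concern.** The sentence moves from 52 and 25% to 68 as if by calculation, and a reader who repeats the calculation does not get 68. The number randomised is the figure that sites, funder and ethics committee work to, so it should follow from its stated inputs. Here it falls slightly short of the completer target that it is meant to protect.

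The wording adds a second, related difficulty. Recruitment is described by a maximum and by a completer count, joined by an "or" that can be read in more than one way. If the maximum governs, the rounding leaves the trial one expected completer short. If the completer count governs, the shortfall corrects itself, but 68 is then no longer a maximum.

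**Working it through.** **Inputs from the Sample size section:** 52 completers (26 per group); loss after randomisation 25%; recruitment figure 68 (34 per group).

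**Assumptions, needed for power only:** standardised difference d = 0.8 for the large effect, two-sided 5% test, target power 80%. The article states none of these except the 5% level.

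**Step 1. The base figure reproduces.** With d = 0.8, two-sided 5% and 80% power, the exact two-sample t-test calculation gives 25.52 per group, hence 26 per group and 52 in total. This agrees with the article, so the assumptions are plausible, though not confirmed.

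**Step 2. The inflation.** Number to randomise = completers / (1 − loss).
- Total: 52 / (1 − 0.25) = 69.33, rounded up to an even number: 70.
- Per group: 26 / 0.75 = 34.67, rounded up: 35.
- The common shortcut of multiplying does not give 68 either: 52 × 1.25 = 65.
- Rounding 34.67 down gives 34 per group and 68 in total, which is the likely origin of the figure.

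**Step 3. What 68 delivers.**
- Expected completers at 25% loss: 68 × 0.75 = 51 (25.5 per group).
- Loss at which 68 gives 52: 1 − 52/68 = 16/68 = 23.5%.

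**Step 4. Chance of reaching the target if recruitment stops at the number shown.** Each participant is taken to complete independently with probability 0.75 (exact binomial).

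| Randomised | Expected completers | P(at least 52 in total) | P(at least 26 in one given group) | P(at least 26 in both groups) |
|---|---|---|---|---|
| 68 | 51.0 | 45.4% | 51.3% | 26.4% |
| 70 | 52.5 | 61.7% | 62.6% | 39.2% |
| 72 | 54.0 | 75.6% | 72.5% | 52.6% |

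**Step 5. Effect on precision and power.** With equal groups and a common variance, the standard error of the group difference is proportional to 1/√N. Going from 52 to 51 completers therefore widens it by √(52/51) = 1.0098, about 1%, whatever the effect size. Power from the exact t-test at d = 0.8, two-sided 5%:

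| Completers per group | Power |
|---|---|
| 26 | 80.7% |
| 25.5 | 80.0% |
| 25 | 79.1% |
| 24 | 77.4% |

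With 68 randomised at 25% loss, the chance of at least 48 completers in total is 83.7%, so power below about 77% on these assumptions is unlikely.

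Steps 2 to 4 do not depend on effect size, power or sidedness.

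**The case against.** The strongest reply is that this is two patients in 70 (2.9%), on a loss rate that the article itself calls an estimate. A true loss of 23.5% instead of 25% would make 68 exactly right, and nobody can forecast attrition to that precision. The statistical methods section also plans to collect outcomes from participants who stop the exercise programme, to analyse by intention to treat, and to use multiple imputation or Bayesian methods if necessary, so leaving the programme need not mean a lost outcome. All of this stands and keeps the point minor. It does not make 68 the result of the two stated inputs.

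Three stronger readings are tempting, and the article does not support them.

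- *That the cap and the completer target are joint conditions in conflict.* The two are joined by "or": "or until we achieve 52 (26 per group) completed datasets at 6 weeks". Recruitment may end early once 52 have completed, or it may continue until they have. On the second reading 68 does not bind and the rounding does no harm. The shortfall bites only if 68 overrides the completer target, which the text leaves open.
- *That the rounding is why 26 per group would probably be missed.* The 26% chance for both groups is mostly a feature of inflating to an expected value. The correctly rounded 70 reaches 26 in both groups only 39% of the time, and about 72 are needed to pass one half. A single group of 34 reaches 26 slightly more often than not. The fair measure of the rounding is the total: 45% against 62%.
- *That the trial is underpowered because of it.* The change is under one percentage point, and even that figure rests on an effect size and sidedness that the article does not give.

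**Conclusion.** The point holds as a minor arithmetic and wording correction. The stated 68 does not follow from 52 completers and a 25% loss. Strict inflation gives 70, and 68 yields 51 expected completers. If 68 is a hard cap and the loss is 25% and independent between participants, 52 completers are reached with a probability of about 45% instead of 62%. The cost is about 1% in the standard error and, on the assumed d = 0.8 and two-sided 5%, about 0.7 of a percentage point of power (80.7% to 80.0%). The article does not settle which of the two recruitment conditions governs. That is an ambiguity to clear up, not a demonstrated contradiction.

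**What to change.** Change the recruitment sentence so that its figures agree, without adding patients. One way is to say that 68 randomised (34 per group) gives 51 expected completers at a 25% loss. The other is to keep 52 and give the loss allowance as 23.5%. The first leaves the sourced 25% estimate untouched.

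In the same sentence, say which condition governs if 68 have been randomised and fewer than 52 datasets are complete: whether recruitment stops at 68 or continues. Keep the completer condition. Removing it and stopping at 68 regardless would fix the shortfall in place and take out the one clause that could make it good.

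The cost is a sentence or two of text. The stated figure becomes very slightly less favourable, and no procedure or analysis changes.

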### Recruitment strategies

Strategies to optimise recruitment to the trial will be implemented throughout the trial, and will include: adoption into a clinical trial network (Northern Ireland Clinical Research Network) to facilitate access to dedicated research staff trained in research methods and effective patient tracking procedures between Health and Social Care Trusts in Northern Ireland; weekly contact with recruitment sites to ensure timely resolution of patient eligibility queries; and early identification of reasons for patient decline and mechanisms to minimise patient barriers to recruitment.

### Standard care

Following ICU admission, standard care consists of discharge to a hospital ward to the care of the ward consultant, and the patients are no longer under the care of the critical care team. They are provided with appropriate medical and nursing care, and with referral to other disciplines as necessary. Once mobile and able to return home to a carer or another facility they are discharged from hospital. Participants randomised to the standard care group will receive no additional support to address potential problems specific to critical illness from the study.

### Intervention (exercise programme)

Participants randomised to the intervention group will complete three exercise sessions per week (two sessions of supervised exercise and one unsupervised session) for 6 weeks. Supervised sessions will take place in a hospital gymnasium or, if this is not possible, in the participants home and the unsupervised session will take place at home. Participants will be informed that they can invite a relative or carer to attend the sessions. The selection of a supervised mostly outpatient-based structured exercise programme is important in this study to promote participant confidence in their ability to exercise in a group setting with people with similar problems and experiences of critical illness, and at the same time facilitate an appropriate level of monitoring and safety [20].

A circuit of exercises will be used to provide interval training for up to 60 minutes and this will include rest periods and an aerobic component [19-23]. The programme of exercise will be delivered by trained physiotherapists. It will consist of a warm-up period, a circuit of 10 arm, leg and whole body conditioning and strengthening exercises, followed by an additional period of aerobic exercise (for example, walking, cycle ergometry or treadmill walking) to maintain moderate breathlessness, and finally by a cool-down period and relaxation. Although the programme is standardised it will be tailored to the capability of each individual participant and exercises will be progressed to maintain a level of moderate breathlessness [24]. Strengthening exercises will be included, using higher repetitions and sets and an increase in weight for progression. The aerobic exercise can be based, for example, on the patient’s heart rate and/or the results of the incremental shuttle walk test measured at baseline assessment. All participants will be asked to rest for 10 minutes following cessation of the exercise programme.

Participants will be provided with a written and illustrated exercise manual which facilitates completion of their exercise programme during supervised and unsupervised sessions. The exercise manual has been developed and reviewed by patient representatives, physiotherapy clinicians and the research team. It contains information on the importance of exercising after critical illness, safety advice relating to exercise and information on ‘how you should feel when you exercise’ which details the Borg breathlessness scale [24], as well as a written plan to support completion of the exercises when the participant is at home. Adherence with the sessions will be recorded on a weekly basis using a diary. This approach has been successfully used in a previous exercise-based trial [19]. At the end of the 6-week programme, participants will receive a short consultation to set goals relating to continuing exercise at home and advice to follow their set goals and use a diary to support continued self-directed exercise and physical activity.

